### Sample size

Sample size has been calculated based on a projected effect size for each intervention of mid-range, moderate magnitude (*d* = 0.45) for the primary outcome at 6-month follow-up, based on findings of well-conducted previous trials of parenting interventions for child behavioural disturbance [23, 41–43]. With alpha at 0.025 (due to two pair-wise comparisons (i.e. between DBS and Control, and between ACT and Control), and beta at 0.20, each of the three trial arms requires a minimum of 104 participants (allowing for 10% attrition to the 6-month follow-up). To allow for identification of potentially smaller effects at 6 months, and continued follow-up of the trial participants in later phases of development, a sample size of 369 is being recruited in total.

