### Recruitment and randomisation

Having identified the eligible sample, each family is being contacted by a recruiter in their own home. The study is explained to the mother who is then invited to take part.

From the 2015 cohort, 770 children met all the initial inclusion criteria above before being contacted in their homes. This sample was divided into 11 localities, each comprising approximately 70 families. Within each area, families are being invited to participate in the study (after confirming eligibility) in order of proximity to the intervention centre. Then, following consent and baseline evaluation, mother-child pairs are being randomised to one of the three study groups. This is being effected centrally (i.e. from the Federal University of Pelotas Centre for Epidemiological Research), minimising for child age, sex, level of harsh parenting at age 2 years, and child aggression at age 2 years (all binary variables). This process is being repeated serially across the 11 areas. The interventions are being delivered within public nursery/primary schools within each recruitment area. Assessments are being made at the Federal University of Pelotas Centre for Epidemiological Research (Fig. 1).

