Additional secondary outcomes will be measured at the 4-week post-intervention assessment (#1–4 below) and at the 6-month follow-up (#5–8).Positive parenting will be assessed using the PAFAS Questionnaire, and videotaped sensitivity and reciprocity during book-sharing and free-play parent-child interactions (as successfully used in previous book-sharing trials) [31–33]Parental attitudes about corporal punishment will be assessed using by the Deater-Deckard Study Questionnaire [59]Parental stress will be assessed using the Perceived Stress Scale [60] and Pelotas questions on parenting stressParental and child chronic stress will be assessed by cortisol from hair samples [61–65]Child attention will be assessed using the Strengths and Difficulties Questionnaire [66] and the Card Sort task from the Early Years Toolbox [67]Child executive functions/self-control will be assessed using the Go no Go task from the Early Years Toolbox [67], the Block Design task, and assessor ratingsChild emotion recognition will be assessed using Denham’s puppet task [68]Child empathy/theory of mind/altruism will be assessed using the Em-Que Parent Questionnaire measure [69], the Help task [70], the Dictator Game [71], and the Sally-Anne task [72]

All the outcome measures specified above are being taken at baseline, except the Dictator Game measure of altruism and the Card Sort Game, which were judged to be less amenable to repeat application over a short period of time, and the Sally-Anne task (for empathy, the Triangle task [73] is being used at baseline, but concerns about how well it is functioning require an additional measure for follow-up)

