## Data analysis

Data analysis will be completed by a designated statistician, [name] from the Oxford University Department of Primary Care Medicine, who will work independent from study investigators. Group baseline differences will be investigated including socio-demographic data, such as child sex, and household factors (e.g. income, relationship status), and study outcomes.

The primary and secondary outcomes will be analysed using linear mixed models, which can account for repeated assessments within individuals (for outcomes measured at multiple time-points). Intervention effects will be assessed at post intervention and follow-up and will be adjusted for child’s age, sex, and baseline scores (where applicable). Further socio-demographic factors may also be investigated as covariates. If the necessary assumptions of the models do not hold, suitable alternative models will be fitted. Intention-to-treat analysis will be used to examine intervention effects. Sensitivity analyses will examine if intervention effects maintain for measures that are not dependent on parent report, which may be biased because parents are not blind to the interventions.

The amount and pattern of missing data will be examined and will be addressed using multiple imputation where appropriate. Due to the multiplicity of comparisons, caution will be used in interpreting results of secondary outcome comparisons. No single *p* value will be interpreted in isolation and all findings will be considered together to obtain the full picture of the intervention effects on the different outcome measures.

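### The stated covariate list omits two of the four minimisation factors (age-2 harsh parenting and age-2 aggression), so standard errors tend to be slightly too large and a little power is lost

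*Protocol article*

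**What the plan says.** Recruitment and randomisation: allocation is central, "minimising for child age, sex, level of harsh parenting at age 2 years, and child aggression at age 2 years (all binary variables". The same section divides the eligible children into 11 localities and adds: "This process is being repeated serially across the 11 areas". Area is not in the list of minimisation factors.

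Data analysis: intervention effects are adjusted for the child's "age, sex, and baseline scores (where applicable". Then: "Further socio-demographic factors may also be investigated as covariates". The models are "linear mixed models, which can account for repeated assessments within individuals"; no term for area is mentioned.

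Assessments: "All the outcome measures specified above are being taken at baseline, except the Dictator Game" and two other named tasks (Card Sort and Sally-Anne). The aggression measures are therefore available at baseline. Table 3 shows no baseline tick for those three tasks or for the search of child protection records, which forms part of a main secondary outcome.

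**The concern.** Minimisation makes the arms more alike on the chosen factors than simple randomisation would, so the true sampling variance of the treatment difference falls. A model that leaves out a prognostic balancing factor puts that factor's variance back into the residual. Its standard error then describes a less well balanced trial than the one that was run. Intervals are too wide, tests are conservative, and precision built into the allocation is not used.

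The omitted factors are plausibly prognostic on the trial's own account. The Background gives the reduction of harsh parenting as one of two routes to less child aggression. Eligibility was set partly on age-2 aggression. Harsh parenting and aggression also appear among the potential moderators. The optional extra covariates do not close the gap, because they are socio-demographic and not committed to.

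Lost precision matters here because the sample was raised from 3 × 104 = 312 to 369 partly to detect effects smaller than the planned one.

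**Working it through.** **1. The plan's own figure.** Inputs from Sample size: d = 0.45, "With alpha at 0.025 (due to two pair-wise comparisons", power 0.80, 10% attrition. Taking the test as two-sided (not stated):

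n = 2[(2.2414 + 0.8416)/0.45]² = 93.9, so 94 per arm. With attrition, 93.88/0.9 = 104.3, or 94 × 1.1 = 103.4. The stated 104 is reproduced, without any covariate adjustment.

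With 369/3 = 123 per arm (equal allocation assumed) and 10% attrition, 110.7 per arm are analysed. Unadjusted power at d = 0.45 is 86.6%.

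**2. Analytic effect of the omission.** Let R² be the share of residual variance, after the stated covariates, that the omitted balanced factors explain. The documents give no value, so a range is assumed.

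- Model SE / true SE = 1/√(1 − R²)
- True type I error = 2[1 − Φ(2.2414/√(1 − R²))]
- Power, factors omitted = Φ[(d/SE − 2.2414)/√(1 − R²)]
- Power, factors included = Φ[d/(SE√(1 − R²)) − 2.2414]

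Here SE = √(2/110.7) = 0.1344 and d = 0.45:

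| Assumed R² | SE too large by | True type I error (nominal 0.025) | Power, omitted | Power, included |
|---|---|---|---|---|
| 0.01 | 0.5% | 0.0243 | 86.7% | 86.9% |
| 0.02 | 1.0% | 0.0236 | 86.8% | 87.3% |
| 0.05 | 2.6% | 0.0215 | 87.2% | 88.4% |
| 0.10 | 5.4% | 0.0181 | 87.8% | 90.1% |

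With only 94 analysed per arm, the power pairs are 80.2% and 80.5% at R² = 0.01, and 81.3% and 84.4% at R² = 0.10.

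**3. Simulation.** The set-up was 369 children, 10% attrition and 3,000 runs per scenario. Minimisation was run within 11 areas with a random element. The outcome had a coefficient of 0.5 on the baseline score, and that score correlated 0.4 with the scale underlying age-2 aggression. The stated model was compared with the same model plus both age-2 factors and area. Prognostic strengths are assumptions: coefficients of 0.1, 0.2 and 0.3 for each age-2 factor, paired with area ICCs of 0.01, 0.03 and 0.05.

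| Scenario | Type I error, stated / full | Power at d = 0.35, stated / full | Power at d = 0.45, stated / full |
|---|---|---|---|
| Weak | 0.0200 / 0.0233 | 77.7% / 77.9% | 94.3% / 94.3% |
| Moderate | 0.0213 / 0.0237 | 75.8% / 78.2% | 94.4% / 95.0% |
| Strong | 0.0200 / 0.0253 | 75.9% / 80.7% | 93.6% / 95.3% |

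The stated model's mean SE was 0.6% to 4.9% above the empirical SE. Power is higher than in step 2 because both models use the baseline score.

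Two cautions apply:

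- Monte Carlo error is about √(0.025 × 0.975/3000) = 0.003 for the type I error, so 0.020 is not sharply separated from 0.025.
- Part of the simulated loss comes from area. In the strong scenario each evenly split binary factor contributes 0.3²/4 = 0.0225, so the two give about 0.045 (ignoring their correlation) against 0.05 from area. If minimisation was not run separately by area, the loss from the two named factors alone is smaller.

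**4. Outcomes with no baseline score of their own.** For child protection records, Card Sort, Dictator Game and Sally-Anne, the stated list reduces to age and sex. No baseline score then absorbs any of the variance due to the age-2 factors.

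**The case against.** The strongest reply is that the effect is small and on the safe side. Aggression is re-measured at baseline, and age-2 aggression was itself rated on a scale from the ELDEQ study, whose items recur at baseline. Range is restricted too, because children with very low age-2 aggression were excluded and only low-income families enter. Both facts pull down the residual R². Assuming 20% would give an SE error of 1/√0.8 − 1 = 11.8%, but nothing in the documents supports so high a value after baseline adjustment. This part of the reply stands and limits the size.

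A second reply is that the article is condensed and the covariate list may be completed elsewhere. That is possible. Still, the article does state a list, and it does not match the allocation stated in the same article.

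Some stronger readings are tempting but unsupported:

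- **Area as a design factor.** A reader might infer that allocation was stratified by area. The text names four factors without area, and serial repetition may only describe roll-out.
- **A selectable primary estimate.** A reader might infer that covariates will be picked after baseline imbalance is seen. The text describes baseline comparisons and optional covariates separately and never links them, and an independent statistician does the analysis.
- **A net conservative analysis.** Both interventions are delivered to groups of mothers. Correlation within those groups could push the model-based SE the other way. This was not computed.

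**Conclusion.** The mismatch is real: two of the four minimisation factors are outside the committed adjustment set, and the optional covariates do not cover them. Taken alone, the omission makes model-based SEs about 0–5% too large and puts type I error at roughly 0.020–0.025 against 0.025 (0.018 at the top of the analytic range). It costs about 0–3 power points at d = 0.45 and up to about 5 at d = 0.35.

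These sizes rest on assumed prognostic strength, on equal allocation, and on no clustering by delivery group. The simulated figures also assume allocation within area. A reader might infer that the trial is underpowered or that false positives are inflated. Neither follows: the 80% was calculated without covariates and is exceeded at 369, and the error from this source is conservative. Omitting balanced factors from a linear model does not bias the estimate. The point is a modest improvement worth making, not a threat to validity.

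**What to change.** In Data analysis, state that the primary and secondary models adjust for all four minimisation factors (child age, sex, age-2 harsh parenting, age-2 aggression) and for the outcome's baseline score where one exists.

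State also whether minimisation was run separately within each of the 11 areas. If it was, include area as a fixed or random effect.

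Report any model with further socio-demographic covariates as a labelled sensitivity analysis, not as the primary result.

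The two binary factors cost 2 degrees of freedom, and area as a fixed effect costs 10 more, out of about 369 × 0.9 = 332 analysed. The age-2 variables and area are already held because recruitment and allocation use them, so no new data are needed and no participant is affected. The change should be recorded before outcome data are examined by arm.

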### Mediator analyses

Mediator analyses will aim to identify active components of the interventions and elucidate the pathways to change. To this end, the following question will be examined: whether the impact of the interventions on child aggression is mediated by improvements in child cognition and by reductions in harsh parenting.

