#### Procedures

All mother/child pairs are assessed on three occasions: at baseline, 4 weeks following the intervention, and 6 months post intervention. For the baseline assessment, mothers are contacted by study recruiters and the study is explained to them. It is emphasised that participation is entirely voluntary and that non-participation carries no consequences. A suitable time for them to come to the Research Centre for assessment by the data collector is arranged. On arrival at the assessment session, consent is explained again and caregivers provide written consent for both themselves and their child. Assessments take 2 h and 20 min, on average. They comprise specific assessments of the child (e.g. language assessment), questionnaires completed by the caregiver (e.g. child behaviour), and filming the caregiver and child in interactive tasks (e.g. during book-sharing). There are breaks for refreshment and, if the child shows signs of tiredness or distress, the session is interrupted or, if necessary, terminated. Participants are given a small gratuity for contributing their time to the study. Similar procedures are followed for the subsequent two assessment waves. To prevent assessor bias, assessments of children and caregivers are being carried out blind to group allocation, with the at random allocation being conducted separately at the end of the baseline assessment. Participants are explicitly asked to not reveal their allocation to the data collectors in follow-up assessments. All coding of video material will be made blind to allocation.

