The primary outcome is child aggression at the 6-month follow-up assessment, measured by parental report, and direct observation. The parent report measures include two questionnaires: the Aggression sub-scale of the Child Behavior Checklist (CBCL) [55] and items on aggression from the ELDEQ Study Questionnaire [39]. Three observational measures are being used: child response to a frustration task (from the *Laboratory Temperament Assessment Battery* for preschool children, www.uta.edu/faculty/jgagne/labtab), and child behaviour during ‘Don’t touch’ and ‘Clean Up’ tasks [56, 57]. The multiple measures of aggression will be combined into at least one latent variable for analysis of the primary outcome, and the independent trial statistician will decide if a single variable or multiple latent variables are required (for example, one for observed aggression and one for reported aggression).

The two main secondary outcomes will be measured at the 6-month follow-up. All relevant measures are being administered to the whole trial sample, but effects are hypothesised to be specific to DBS or ACT, as outlined above:Child language will be assessed using the Test of Receptive and Expressive Vocabulary (Teste de Vocabulário Auditivo e Teste de Vocabulário Expressivo http://memnon.com.br/produto/teste-de-vocabulario-auditivo-e-teste-de-vocabulario-expressivo/)Harsh and abusive parenting will be assessed by parent self-report, using the PAFAS Questionnaire [58], the Juvenile Victimisation Questionnaire (http://www.unh.edu/ccrc/jvq/index_new.html), by direct observation during the ‘Don’t touch’ and ‘Clean Up’ tasks [56, 57], and by searches of child protection service records

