### Moderator analyses

Moderator analyses will be conducted to investigate whether certain groups respond differently to the interventions. In addition to the potential mediators listed above, we will examine the impact of number of intervention sessions attended. Potential mediators and moderators of the intervention will be examined using mixed linear models or structural equation modelling, as appropriate.

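### Neither named mediator is measured after baseline and before the 6-month aggression visit, so the direction of any mediation rests on an untestable assumption

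*Protocol article*

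**What the plan says.** The protocol article's Mediator analyses section sets one question: "whether the impact of the interventions on child aggression is mediated by improvements in child cognition and by reductions in harsh parenting". Its stated purpose is to explain how the interventions work. The Moderator analyses section adds the method: "Potential mediators and moderators of the intervention will be examined using mixed linear models or structural equation modelling, as appropriate".

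The timing is fixed in the Assessments section and in Table 3:

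- Outcome: "The primary outcome is child aggression at the 6-month follow-up assessment".
- Child language and harsh parenting: "The two main secondary outcomes will be measured at the 6-month follow-up".
- Everything else: "Additional secondary outcomes will be measured at the 4-week post-intervention assessment (#1–4 below) and at the 6-month follow-up (#5–8"). Attention, executive function, emotion recognition and empathy/theory of mind are items 5 to 8, so they fall at 6 months.
- In Table 3, no harsh-parenting or child-cognition row has a post-intervention tick. Most have baseline and follow-up ticks. Card Sort, Sally-Anne and the child protection record searches are follow-up only.

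A visit between treatment and outcome does exist. The Procedures section says: "All mother/child pairs are assessed on three occasions: at baseline, 4 weeks following the intervention, and 6 months post intervention". PAFAS, which is also one of the harsh-parenting measures, is listed for that visit under another heading: "Positive parenting will be assessed using the PAFAS Questionnaire, and videotaped sensitivity and reciprocity during book-sharing and free-play parent-child interactions".

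**The concern.** Randomisation identifies the effect of each programme on harshness and, separately, on aggression. It does not identify which of the two drives the other when both are first seen after baseline at the same visit. An aggressive child can provoke harsh parenting, so the reverse direction is a real alternative. Under that alternative, a product-of-coefficients or structural model returns a non-zero indirect effect although harshness does nothing to aggression.

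The Data analysis section says that intervention effects "will be adjusted for child’s age, sex, and baseline scores (where applicable"). Carried into the mediation model, that adjustment would not help, because the ambiguity concerns change after baseline. At stake is the trial's account of why the programmes work, which Mediator analyses does not qualify as associational. A later analysis plan could change the wording, but it could not supply 4-week values that were never collected.

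**Working it through.** **1. Plan figures used.** The plan gives no mediation figure. Its effect size, d = 0.45, is used below, so its sample size was checked first. With two-sided alpha 0.025 and power 0.80, n = 2(2.241 + 0.842)²/0.45² ≈ 94 evaluable per arm. Allowing 10% attrition gives 94 × 1.10 ≈ 104, or 94/0.90 ≈ 105. The plan states 104, so there is no error there. Assuming equal allocation, 369/3 = 123 per arm, and 123 × 0.9 ≈ 111 evaluable, or 222 in one comparison with Control.

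**2. Timing.**

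| Variable | Baseline | 4 weeks | 6 months |
|---|---|---|---|
| Child aggression (outcome) | yes | no | yes |
| Harsh parenting (mediator) | yes, except record searches | no | yes |
| Child cognition (mediator) | most measures | no | yes |
| Positive parenting, including PAFAS | yes | yes | no |

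**3. Size of the artefact.** This is a model with assumed values and no effect of mediator on outcome. X is treatment, Y aggression, M harshness and r the assumed reverse slope. Errors are independent with unit variance.

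- Y = −0.45X + e₁
- M = −dX + rY + e₂, where d is the direct treatment effect on harshness

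The analyst estimates:

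- treatment on mediator: a = −(d + 0.45r)
- mediator on outcome given treatment: b = r/(1 + r²), because within arm Cov(M,Y) = r and Var(M) = 1 + r²
- false proportion mediated = ab/(−0.45) = r(d/0.45 + r)/(1 + r²)

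| Assumed direct effect d | r = 0.2 | r = 0.3 | r = 0.4 |
|---|---|---|---|
| 0: r²/(1 + r²) | 0.04/1.04 = 4% | 0.09/1.09 = 8% | 0.16/1.16 = 14% |
| 0.20 SD | 12% | 20% | 29% |
| 0.45 SD: r(1 + r)/(1 + r²) | 0.24/1.04 = 23% | 0.39/1.09 = 36% | 0.56/1.16 = 48% |

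The true value is 0% in every cell.

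**4. Does baseline adjustment remove it?** A simulation with 111 per arm, d = 0 and adjustment for baseline mediator and baseline aggression gave 4%, 8%, 20% and 33% for r = 0.2, 0.3, 0.5 and 0.7. Both paths were significant (|z| > 1.96) in 10%, 18%, 39% and 60% of trials. With d = 0.45 and the same adjustment, r = 0.2, 0.3 and 0.4 gave 23%, 35% and 49%. Adjustment leaves the artefact in place.

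**5. Does an earlier mediator remove it?** In the d = 0 simulation, a mediator taken before aggression had changed gave a false indirect effect of about zero, with joint significance in at most 0.4% of trials. That is the ideal case. Aggression is not measured at 4 weeks, so the plan cannot show that it had not yet changed.

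**The case against.** **Can the analysis answer nothing?** A reader might infer this, but it goes too far. Any mediation analysis in a trial that randomises only treatment needs untestable assumptions, because mediator and outcome can share causes even when the mediator comes first. Concurrent measurement adds one more assumption, about direction. An association consistent with mediation can still be reported.

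**Are the larger percentages the size of the problem?** The documents do not support any single figure. The slopes are assumed, and most of the bias in the bottom row of the table comes from assuming a 0.45 SD direct effect on harshness. That row is relevant, because the second hypothesis expects ACT to reduce both harshness and aggression, but the top row is equally possible. The figures also concern harshness only. No separate figure is offered for cognition.

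**Will harshness and aggression from the same task be paired?** Both are scored in the 'Don't touch' and 'Clean Up' tasks, so one might infer this. The plan does not commit to it. Both constructs have other sources, and a structural model can allow for shared method variance. It is a point to guard against in the analysis plan.

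**Does a 4-week mediator cure the problem?** Only in part. That visit follows 8 or 9 weekly sessions and a further 4 weeks, so aggression may already have changed and fed back on harshness. The sensitivity and reciprocity ratings taken there are correctly ordered, but they are not the mediators that the plan names.

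**Was it too late?** At submission on 16 August 2018, 304 of 369 were recruited. Delivery began in July 2018. The shorter programme spans at least 7 weeks from first to last session, and 7 + 4 = 11 weeks, while 1 July to 16 August is under 7 weeks. No 4-week visit was yet due. By publication in May 2019 the window may have closed, which is why the fix has a second part.

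**Conclusion.** The point holds as a limit on interpretation that a small change would ease. After baseline, both named mediators are first measured at the visit that measures the outcome, so the direction of the link is assumed and not tested. The false proportion mediated runs from about 4% to 14% (no direct effect on harshness) up to about 23% to 48% (direct effect 0.45 SD), for assumed reverse slopes of 0.2 to 0.4 and unit error variances. The timing facts come from the article; the slopes and the direct effect on harshness are assumptions. The primary comparison and the separate estimates of effect on harshness and cognition are unaffected. Label: cheap improvement.

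**What to change.** 1. At the 4-week visit, collect and score the PAFAS harsh-parenting items with the positive-parenting items already scheduled. The article does not say whether the whole questionnaire is given there. If it is, only scoring is needed.
2. Use that score as the mediator of 6-month aggression, adjusting for baseline harshness and baseline aggression. State that this reduces reverse causation without eliminating it, because aggression is not measured at 4 weeks.
3. Where mediator and outcome both come from 6 months, report a concurrent, exploratory association. This covers every cognition measure, and harshness too if the 4-week items cannot be added.
4. In those analyses, do not pair harshness and aggression scored from the same 'Don't touch' and 'Clean Up' tasks.
5. Reserve the ordered test for 6-month mediators against aggression at the later cohort waves that the Abstract and Discussion already intend.

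The cost is a few minutes of the mother's time at an existing visit, some wording, and a weaker claim for the cognition path until later waves report.
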